#### 2.4.2. Cost-effectiveness.

Costs related to the implementation of the TP will be systematically collected. These will include personnel costs associated with the time investment of healthcare professionals involved in the program (e.g., physician, nurses, psychologists, dieticians, and diabetes educators), as well as costs related to multidisciplinary team meetings. In addition, material costs will be considered, including printed educational materials and other resources used within the intervention. Healthcare resource use will be estimated using published data on healthcare utilization patterns, combined with unit costs derived from the National Institute for Health and Disability Insurance (NIHDI) nomenclature of healthcare services. This approach will allow estimation of healthcare costs associated with outpatient visits, hospitalizations, and other reimbursed services. Health outcomes will be derived from the EQ-5D-5L utility values. Together with cost data and transition probabilities, these will serve as input to the model. Quality-adjusted life years (QALYs) will be calculated as an outcome of the analysis and, together with costs, will form the basis for the TP’s cost-effectiveness evaluation.

#### 2.4.3. Process evaluation.

AYAs, families, and healthcare professionals who participated in the TP will be invited to a process evaluation, aimed at assessing both the implementation of the TP and how it was received, in accordance with the Medical Research Council guidance [34]. This evaluation is essential to contextualize findings from the effectiveness study, helping to explain why and when the TP was or was not successful. Several programme dimensions will be examined, including: intervention fidelity (the extent to which the TP was delivered as intended with consistent quality), dose (the extent to which the TP was delivered by healthcare providers and received by patients and families), reach (the proportion and characteristics of patients who participated), context (factors that facilitated or hindered TP uptake), and change (changes made by care team during implementation) [35]. Data will be collected both during and at the end of the programme using a mixed-method approach, combining quantitative and qualitative data to enable triangulation and provide comprehensive coverage of all program dimensions:

**Observations.** Longitudinal non-participatory observations of outpatient visits will be conducted using a structured checklist to assess programme fidelity across three intervention components (key moments 1–3). For each chronic condition, two observations per measurement moment will be conducted in the intervention group (total n = 18), ensuring variation across hospital settings, consultation type, and participant characteristics.

**Individual transition plans.** Data from the individualized transition plans will be extracted to evaluate fidelity, participant engagement, adherence, and overall quality of programme delivery, including dose delivered and dose received.

**Interviews.** Semi-structured interviews (15–30 minutes) will be conducted at the end of the intervention to explore experiences, perceived facilitators and barriers, and contextual factors. A total of five AYAs will be interviewed, including four from the intervention group (representing the three diagnostic groups) and one from the control group. In addition, five healthcare professionals and three parents will be interviewed. Interview data will be used to further explore programme delivery and uptake, as well as contextual influences affecting implementation. An overview of the interview topic guide can be found in Table 1.

**Table 1 pone.0353932.t001:** Topic guide that will be used for the process evaluation of the COCCOS intervention.

Topics	Main questions

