#### 2.3.2. Participants.

The study will focus on three common chronic childhood-onset conditions: type 1 diabetes, asthma, and obesity. The three diagnostic groups will be included to ensure variability and representativeness. Eligibility criteria for the intervention group include: being 17 years old, having a diagnosis of one of the target conditions, at least one paediatric outpatient visit in the past 12 months, Dutch-speaking, and a planned transfer to adult care within 12 months. Participants in the control group are aged 17,5–18 years, Dutch-speaking, with a planned transfer to adult care in the near term. Patients with severe mental, cognitive, and/or neurological impairments are excluded. At UZ Ghent, only type 1 diabetes patients will be included, while at UZA, patient with asthma and obesity patients will be included.

Based on reference data from previous studies, the intervention target was defined as an improvement in the primary outcome corresponding to a one standard deviation (SD) increase in the TRAQ score [24–26]. This target was set assuming 90% power, an effect size of d < 0.6, and a significance level of α = 0.05. A power analysis conducted using G*Power 3.0 indicated that 22 participants per group (intervention and control) would be required. Considering the heterogeneity of the AYA population and comparable disease complexity across subgroups, this sample size was applied at the population level, resulting in a total required sample of 44 participants. To account for an anticipated attrition rate of 25% over a 24-month follow-up period [27], as well as potential recruitment challenges, the total target sample size was increased to 55 participants. Accordingly, a minimum of 28 participants per group (intervention and control) should be recruited.

For the process evaluation, all participating AYAs, their families, and involved healthcare providers will be invited to complete quantitative assessments. A purposive subsample will be selected for qualitative evaluation to capture variability in experiences and perspectives, ensuring representation across conditions, sites, and roles in the care process.

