**Healthcare professionals**	
*Experience with the program and protocol*	- Can you describe your experience with implementing the transition program and its protocol? Which components were most useful or less feasible?
*Organization and collaboration*	- How would you describe coordination within the team and collaboration between pediatric and adult care?
*Use of tools in practice*	- What is your experience with the use of the individualized transition plan?
*Barriers, facilitators, and feedback*	- What factors facilitated or hindered implementation? What feedback did you receive from patients/families, and how was it used?
*Support, evaluation, and sustainability*	- Did you feel sufficiently supported? How would you rate the program (0–10) and why? Is it feasible to implement sustainably in your service?

**Experience survey.** An experience questionnaire, including a brief set of sociodemographic items (e.g., age, sex, socio-economic status), will be administered electronically to AYAs (all participants), family members (where contact details are available), and healthcare professionals (all) at the end of the intervention to assess perceptions of the TP and completion of intervention components. Survey data will be used to assess dose received, operationalized as satisfaction with the intervention. In addition, the results will inform and guide the interviews, with certain topics explored in greater depth during the interviews. Table 2 provides an overview of the questions included in the experience survey.

**Table 2 pone.0353932.t002:** Overview of the questions included in the experience survey for the process evaluation of the COCCOS intervention.

Section	Content questions	Response format

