**Healthcare professionals**		
*Socio-demographic information*	- Gender - Profession - Years of experience	- Male/female/other - Open-ended - Years
*General evaluation*	- Was the programme manual sufficient? - Was the individualized transition plan discussed during consultations? - Did contact moments add value for AYAs and parents? - Were AYAs and parents prepared for transition? - How easy/difficult did you found the individualized transition plan? - How easy/difficult did you found the brochures? - How satisfied were you with the COCCOS intervention? - Would you continue implementing the programme? - Do you have additional suggestions?	- Categorical + open-ended - Categorical + open-ended - Categorical + open-ended - Categorical + open-ended - Likert scale - Likert scale - Likert scale - Categorical + open-ended - Open-ended

**Registration form.** Recruitment of hospital departments and eligible patients will be monitored using a registration form, with reasons for non-participation documented where possible to inform assessment of recruitment processes and programme reach.

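### The experience survey and all interviews come at the end of the programme, and interview selection does not consider completion, so satisfaction and acceptability will lean towards completers

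*Protocol article*

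**What the plan says.** Section 2.4.3 of the protocol article gives the process evaluation the task of "helping to explain why and when the TP was or was not successful". Two of its tools ask AYAs and families directly what they thought of the programme, and both are placed at the end:

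- **Interviews.** These "will be conducted at the end of the intervention to explore experiences, perceived facilitators and barriers, and contextual factors". On numbers: "A total of five AYAs will be interviewed, including four from the intervention group (representing the three diagnostic groups) and one from the control group". Section 2.3.2 describes the qualitative subsample as purposive, "ensuring representation across conditions, sites, and roles in the care process".
- **Experience survey.** It is sent electronically to all AYA participants, to family members whose contact details are held, and to all professionals, "at the end of the intervention to assess perceptions of the TP and completion of intervention components". On its use: "Survey data will be used to assess dose received, operationalized as satisfaction with the intervention". The AYA and parent versions in Table 2 ask which contact moments were attended and, in open text, why others were not.

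The remaining sources are the registration form, which covers recruitment and reach "with reasons for non-participation documented where possible", structured observations at key moments 1–3, and data extracted from the individualized transition plans. Section 2.3.2 anticipates 25% attrition over 24 months, and the Discussion lists retention among the parameters to be carried into a larger study.

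**The concern.** A process evaluation that is meant to explain failure as well as success has to hear from people for whom the programme did not work. Some of them will have left before the end, and that is when both direct tools are used. An invitation addressed to all participants is not the same as a response from all participants: someone who withdrew months earlier is less likely to answer an email, and no contact at the point of leaving is described.

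Two features sharpen this. First, satisfaction is the chosen measure of dose received, so selective non-response distorts a core process dimension as well as the opinion data. Second, with only four intervention-group AYA interviews, a selection rule that does not mention completion can easily produce four completers. The AYA topic guide in Table 1 has no question on stopping or on missed contact moments.

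At stake are a satisfaction figure that is somewhat too favourable and thin evidence on leavers' own reasons. Both matter for a study whose declared use is to refine the programme and plan a larger trial.

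**Working it through.** **Inputs from the article (section 2.3.2 unless stated).** Required sample 44; attrition 25% over 24 months; target 55 in total, at least 28 per group; programme length in the intervention group 13–16 months (section 2.3.1).

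**Plan's own figure.** 44 × 1.25 = 55, and 55 / 2 = 27.5, rounded up to 28 per group. This reproduces the stated target. Whether multiplying by 1.25 is the right way to allow for attrition is a separate matter; here 28 serves only as the denominator.

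**Step 1: expected leavers by the time of the survey.** The 25% refers to 24 months, so it has to be scaled to the programme. With a constant loss rate (assumption), loss by month m is 1 − 0.75^(m/24).

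- m = 13: 1 − 0.75^(13/24) = 14.4%; 28 × 0.144 = 4.0 people
- m = 16: 1 − 0.75^(16/24) = 17.5%; 28 × 0.175 = 4.9 people

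So about 4–5 of 28 would have left.

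**Step 2: effect on reported satisfaction.** Assumptions not in the article: 85% of completers are satisfied, 40% or 60% of leavers are satisfied, all completers answer and no leaver does. The survey then shows 85%. The figure for everyone enrolled is (1 − p) × 0.85 + p × s, where p is the loss and s the satisfaction among leavers.

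| Loss p | s = 40% | s = 60% |
|---|---|---|
| 14.4% (13 months) | 78.5% | 81.4% |
| 17.5% (16 months) | 77.1% | 80.6% |

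The overstatement runs from 85 − 81.4 = 3.6 to 85 − 77.1 = 7.9 percentage points.

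**Step 3: if some leavers do answer.** Take the worst cell (p = 17.5%, s = 40%) and let half of the leavers respond. The survey shows (0.8255 × 0.85 + 0.0873 × 0.40) / (0.8255 + 0.0873) = 80.7%, against 77.1% in truth. The gap falls to about 3.6 points. If leavers answered as often as completers, it would disappear.

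**Step 4: what each source can tell about a leaver.**

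| Source | Where engagement stopped | The leaver's own reason |
|---|---|---|
| Experience survey | Yes, if answered | Missed contact moments, if answered |
| AYA interviews | Only if a leaver is selected | Only if a leaver is selected |
| Transition plans | Yes | Little |
| Observations (18 sampled visits) | Partly; a visit that does not happen cannot be observed | No |
| Professionals' survey and interviews | Partly | Second-hand |
| Registration form | No; it concerns recruitment | Only reasons for not joining |

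**The case against.** The strongest reply is that the article provides more than the timing of two tools suggests.

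- The survey is electronic, needs no attendance and is addressed to every participant. Its items on missed contact moments presuppose respondents who did not complete everything. AYAs who skip a key moment or stop the programme may still be study participants who can be emailed; only those who withdraw from the study may be out of reach, and section 2.6 protects their right to leave.
- The purposive subsample is meant to capture varied experiences and perspectives. That leaves room for non-completers even though they are not named.
- Data are collected during the programme as well. Transition plans are filled in as it proceeds, and at key moment 4 the researcher contacts the AYA to evaluate the transition.
- A journal article condenses the full protocol, which may well hold a log of withdrawal dates and reasons.

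Most of this stands, and it rules out three stronger readings. A reader might infer that reasons for dropping out are recorded nowhere. The documents do not support that: reasons for missed contact moments and for not joining are both collected, and the absence of a withdrawal-reason field from an article is no finding. A reader might infer that the evaluation cannot tell when the programme failed; transition plans and observations can show where engagement stopped. A reader might also take 25% of 28, which is 7, as the number missing; that applies a 24-month rate to a programme of 13–16 months.

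The reply does not remove the stated timing of the survey and interviews or the stated selection criteria. The article fixes both, and both favour people who are still engaged at the end. Key moment 4 comes after transfer, so it too falls at the end.

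**Conclusion.** The point holds as a modest one. As written, satisfaction, and with it dose received, and acceptability will lean towards completers, and the evaluation will hear little of leavers' own reasons. It does not follow that acceptability will come from completers alone or that drop-out will go unexplained.

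The illustrated size is 4–5 of 28 intervention participants unheard and an overstatement of roughly 4–8 percentage points (85% shown, about 77–81% in truth). This rests on a constant loss rate, on assumed satisfaction of 85% and 40–60%, and on no leaver responding. The direction needs only that leavers are less satisfied and respond less often. The size shrinks as more of them answer. Nothing here affects the primary outcome analysis.

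**What to change.** Three small changes to section 2.4.3 and the sampling sentence in section 2.3.2:

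1. **Survey timing.** Send the existing experience survey at discontinuation as well as at the end, clearly voluntary. The follow-up outcome questionnaires already go out by automated REDCap email (section 2.4.1), so this should need only one more trigger. Participants who have already left can be included where their consent allows contact.
2. **Interview selection.** Keep one intervention-group AYA interview per condition and offer the fourth to someone who stopped or missed the joint consultation. Add completion status to the criteria in section 2.3.2.
3. **Reporting.** Give satisfaction separately for completers and non-completers, with the number of responders and of those invited in each group.

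If the full protocol does not already record the date and reason of each withdrawal, one added form field would do so.

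The cost is a survey trigger, a changed selection rule and one extra row in a table, with no additional interviews. The downside is one fewer completer interview. Data collection runs to December 2026 (section 2.1), so the change may still be possible for those who have not reached the end, subject to any ethics notification it requires.

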**Adolescents and young adults (AYAs)**	
*Program experience*	- Can you describe your overall experience with the transition program, including the contact moments (content and frequency)?
*Use of tools and information*	- Did you use your individualized transition plan outside of consultations? What was your experience with it? - What do you remember from the information brochures, and was any important information missing?
*Preparedness for transition*	- To what extent did you feel prepared for the transition to adult care? Why/why not?
*Evaluation and improvement*	- How would you rate the program (0–10) and why? What improvements would you suggest?
**Parents**	
*Program experience*	- Can you describe your overall experience with the transition program, including the contact moments?
*Communication and support*	- Did you feel there was sufficient opportunity to address your and your child’s concerns and questions?
*Use of tools and information*	- Did you or your child use the individualized transition plan outside consultations? What was your experience? What do you remember from the information materials, and was anything missing?
*Impact and preparedness*	- Did you notice any changes in your child during the transition? Did you feel prepared for the transition to adult care? Why/why not?
*Evaluation and improvement*	- How would you rate the program (0–10) and why? What improvements would you suggest?
**Healthcare professionals**	
*Experience with the program and protocol*	- Can you describe your experience with implementing the transition program and its protocol? Which components were most useful or less feasible?
*Organization and collaboration*	- How would you describe coordination within the team and collaboration between pediatric and adult care?
*Use of tools in practice*	- What is your experience with the use of the individualized transition plan?
*Barriers, facilitators, and feedback*	- What factors facilitated or hindered implementation? What feedback did you receive from patients/families, and how was it used?
*Support, evaluation, and sustainability*	- Did you feel sufficiently supported? How would you rate the program (0–10) and why? Is it feasible to implement sustainably in your service?

**Experience survey.** An experience questionnaire, including a brief set of sociodemographic items (e.g., age, sex, socio-economic status), will be administered electronically to AYAs (all participants), family members (where contact details are available), and healthcare professionals (all) at the end of the intervention to assess perceptions of the TP and completion of intervention components. Survey data will be used to assess dose received, operationalized as satisfaction with the intervention. In addition, the results will inform and guide the interviews, with certain topics explored in greater depth during the interviews. Table 2 provides an overview of the questions included in the experience survey.

**Table 2 pone.0353932.t002:** Overview of the questions included in the experience survey for the process evaluation of the COCCOS intervention.

Section	Content questions	Response format
**Adolescents and young adults (AYAs)**		
*Socio-demographic information*	- Age - Gender - Nationality - Parental nationality - Chronic condition	- Years - Male/female/other - Belgian/other - Belgian/other - Obesity/asthma/type 1 diabetes
*Contact moments*	- Which contact moments did you attend? - Why did you not attend certain contact moments? - Did you complete the Ready Steady Go-checklist? - Did the contact moments teach you something? - What do you remember most? - Did you feel prepared for transition after the joint consultation? - What could be improved?	- Categorical - Open-ended - Categorical + open-ended - Categorical + open-ended - Open-ended - Open-ended - Open-ended
*Individualized transition plan*	- Did you consult the individualized transition plan outside consultations? - How easy/difficult did you found the individualized transition plan?	- Categorical + open-ended - Likert scale
*Information brochures*	- Which brochures did you receive? - Did you read the brochures?	- Categorical - Categorical + open-ended
*General evaluation*	- How satisfied were you with the COCCOS intervention? - Would you recommend the programme?	- Likert scale - Categorical + open-ended
**Parents**		
*Socio-demographic information*	- Age - Gender - Nationality - Child’s chronic condition	- Years - Male/female/other - Belgian/other - Obesity/asthma/type 1 diabetes
*Contact moments*	- Which contact moments did your child attend? - Why were certain contact moments not attended? - Did your child complete the Ready Steady Go-checklist? - Did the contact moments teach your child something? - Did the contact moments inform you as a parent? - Did you feel prepared for transition? - What could be improved?	- Categorical - Open-ended - Categorical + open-ended - Categorical + open-ended - Categorical + open-ended - Categorical + open-ended - Open-ended
**Healthcare professionals**		
*Socio-demographic information*	- Gender - Profession - Years of experience	- Male/female/other - Open-ended - Years
*General evaluation*	- Was the programme manual sufficient? - Was the individualized transition plan discussed during consultations? - Did contact moments add value for AYAs and parents? - Were AYAs and parents prepared for transition? - How easy/difficult did you found the individualized transition plan? - How easy/difficult did you found the brochures? - How satisfied were you with the COCCOS intervention? - Would you continue implementing the programme? - Do you have additional suggestions?	- Categorical + open-ended - Categorical + open-ended - Categorical + open-ended - Categorical + open-ended - Likert scale - Likert scale - Likert scale - Categorical + open-ended - Open-ended

**Registration form.** Recruitment of hospital departments and eligible patients will be monitored using a registration form, with reasons for non-participation documented where possible to inform assessment of recruitment processes and programme reach.

